**2. Summary**

Obsessive compulsive disorder (OCD) is a common problem affecting 13% of the population. OCD makes people anxious and unhappy, interferes with everyday activities such as working or looking after relatives and it costs patients, their families and the country a lot of money. OCD rarely improves without treatment. New treatment guidelines were developed by experts in 2005. These guidelines recommend that people with OCD receive a form of psychological help, or talking treatment, called cognitive behavioural therapy (CBT). The guidelines suggest that this CBT might be delivered as a selfhelp approach. In selfhelp, CBT is delivered through a book or computer programme, with some guidance from a mental health professional. Guidance can be delivered over the telephone, by email or face to face.

However, we still do not know which method of selfhelp is most useful, or how useful they are compared to usual care. Our proposed study will test 2 different self help treatments for OCD. These are 1) computerised CBT (cCBT) using an internet delivered OCD treatment package called OCFighter, with telephone or face-to-face support from a mental health professional; and 2) a selfhelp book which helps people to use CBT combined with face to face or telephone support, from a mental health professional. This treatment is called guided self help. Both treatments will be delivered over a 12week period. We want to see if the new treatments (cCBT and guided self help) are effective in the short and longer term. Our study will also find out how satisfied people are with the treatments and which they prefer. Finally, we will calculate the costs of each treatment to OCD sufferers, their families and the NHS.

**3. Planned Investigation**

**3.1 Research objectives:**

Our study aims to:

1. Identify and confirm estimated recruitment rates for an OCD treatment trial via an internal pilot phase aimed at evaluating recruitment rates and primary outcome point.

2. Proceed seamlessly to a full RCT (if recruitment is successful in the pilot phase) to determine:

(a) The clinical and cost effectiveness of two self-managed CBT interventions (cCBT and bibliotherapy) compared to a CBT waiting list in the management of OCD patients in the short term at 3 and 6 month follow up

(b) The clinical and cost effectiveness of self managed therapies plus conventional CBT compared to waiting list plus conventional CBT at 12 month follow up

3. Determine patient compliance and patient and health professional acceptability of the two self managed therapy packages (cCBT & GSH).

**3.2 Existing research:**

Obsessive compulsive disorder (OCD) is a chronic and disabling mental health condition ranked as the 10th leading cause of disability by the World Health Organization [3]. The obsessions and compulsions that characterise this disorder lead to marked distress, are time consuming and significantly interfere with an individual's functioning. The UK prevalence of OCD is 1.1-3.0% [4,5], and unless adequately treated it remains a chronic condition. The NICE guidelines for OCD [6] specify recommendations for the treatment and management of OCD using a stepped care approach. Steps 3-6 of this model recommend treatment options for people with OCD that range from low intensity, primary care-led guided self help to more intensive psychological and pharmacological interventions. Cognitive Behavioral Therapy (CBT) including Exposure and Response Prevention (ERP) is the recommended psychological treatment.

Low intensity interventions are defined as less than 10 hours of therapist time and include CBT (including ERP) with self-managed materials and brief individual CBT by telephone. There is insufficient evidence of the efficacy, cost effectiveness and acceptability of self managed therapy interventions for OCD. Two uncontrolled studies of self help materials with guidance from a therapist [7,8] demonstrate promising results. A trial using CBT delivered by telephone compared with face to face delivery showed similar clinical gains and patient satisfaction [1]. An uncontrolled study [9] which delivered CBT by telephone with self help materials found similar effect sizes as face to face trials.

NICE did not recommend cCBT as a treatment. The commissioning brief requested a trial of self managed therapies with specific reference to cCBT and bibliotherapy. A recent systematic review [10] of cCBT for OCD found only 4 studies, all using the software programme OCfighter (previously known as BT Steps). Results showed significantly better outcomes and less attrition with scheduled compared to unscheduled telephone support. The conclusion of the review found OCfighter to be as good as standard therapist delivered CBT in reducing time spent in rituals and obsessions and in improving work and social functioning. Overall, standard therapist-delivered CBT was more effective than OCfighter but not for those who actually started as opposed to those who failed to begin self exposure therapy.

A key limitation of this work is that all OCfighter evaluations have been conducted by the commercial company who developed the programme. Further, this programme was originally delivered with an interactive voice response (IVR) and workbook. A more recent version, which has not yet been evaluated in an RCT, comprises a web-based platform in conjunction with brief support via telephone, face-to-face or email contact with a mental health worker. A cost effectiveness analysis has been completed [11] with the original BT steps programme but this was not independent from the developers of the commercially produced package. No studies have compared cCBT to bibliotherapy, nor do we know the numbers of people who will not improve with self-managed packages and who will require more intensive CBT. Thus whilst there is some preliminary evidence that self managed therapy packages for OCD can be effective a more robust evidence base of efficacy, cost effectiveness and acceptability framed within UK NHS services is required.

**3.3 Research Methods:**

The HTA brief calls for an evaluation of self-managed therapy packages for Obsessive Compulsive Disorder (OCD) compared to treatment as usual (i.e. waiting for therapist-based cognitive behaviour therapy). The brief highlights the need for a preliminary pilot phase to ensure recruitment targets can be reached. We propose to conduct i) a pilot phase to determine the feasibility of recruiting to a larger trial. If successful in recruitment in the pilot phase we will proceed seamlessly to ii) a full 3-arm trial as stipulated in the brief. We aim to use a commercially available cCBT package (OC-fighter) delivered via the internet and an existing CBT bibliotherapy package. Both of these technologies have the advantage of being accessible to participants at a time and place convenient to them. To achieve our objectives and meet the commissioning brief we have designed a 2-phase study.

**3.3.1 Phase 1: Pilot Phase**:

The commissioning brief recommended a preliminary phase incorporating a pilot phase to ensure that we are able to recruit the numbers needed for a fully powered RCT. Recruitment to mental health trials is routinely problematic and no trial of OCD has as yet been conducted using the numbers that we propose for a fully powered trial. These potential recruitment difficulties may be further compounded by the UK Increasing Access to Psychological Therapies (IAPT) agenda. The additional resources associated with IAPT could mean that waiting lists for conventional high intensity therapist led CBT decrease. However, the true impact of IAPT on waiting lists remains unknown at the national level and any noticeable change in waiting lists may be partially offset by the 30% rise in mental health referrals following the current economic downturn. Therefore an internal pilot phase is needed to both assess recruitment rates and determine the actual length of time potential participants remain on a waiting list before proceeding to a full trial. Although we have explored the length of current CBT list it is crucial that we accurately assess future waiting times during the pilot phase at each of our study sites in order that we can determine the most accurate short-term follow-up assessment point

Three key questions will be answered via the pilot phase

1. Is it feasible to recruit the numbers required for a fully powered RCT in the designated time available?
2. Do participants remain on a CBT waiting list for a sufficient length of time (i.e. at least 3 months) to conduct an evaluation of the short-term clinical and cost effectiveness of self managed therapies?
3. Is it feasible to retain the proposed 6-month outcome assessment for short term clinical effectiveness in addition to a 3-month follow-up assessment?

We will seek to recruit 153 patients who meet our inclusion criteria (section 3.6) and randomise to i) cCBT, ii) guided self help (bibliotherapy) or iii) CBT waiting list. We will recruit from all 4 of our clinical sites (Manchester, York, Sheffield and East Anglia). Our full trial procedures will be mirrored in the pilot study. Within the pilot phase we will also modify the Adult Service Use Schedule (AD-SUS) to ensure it adequately captures resources appropriate to OCD, as described in Section 3.11 below.

***Criteria for successful recruitment:*** The success of our pilot will be based on reviewing a number of key indicators, one of which is recruitment. We aim to recruit approximately 153 participants in the pilot study and should we achieve or surpass this target then we will accept that we have met our recruitment target. Should we have a significant shortfall however, we will investigate and report the reasons for this to assess whether or not these are transient (e.g. a delay in research governance) that will not lead to a recruitment reduction overall or permanent (e.g. a lack of sufficient consenting patients). Depending on the reasons we will make a recommendation to our independent TSC, and through them to the HTA who will make the decision as to whether the trial should proceed.

***Procedure to proceed to full trial:*** If we are successful in meeting our criteria for recruitment at the end of our pilot study we will proceed to a full trial with permission from the HTA.

**3.3.2 Phase 2: Full RCT:**

If successful in recruiting to target in the pilot study (153 patients in 9 months) and with agreement from the HTA we will proceed seamlessly to a full RCT including a concurrent economic evaluation. This will be a multi-centre fully randomised controlled trial to evaluate 2 self managed packages (cCBT and bibliotherapy) compared to waiting list prior to therapist-based CBT.

The key objectives of our study are to determine:

1. The clinical and cost effectiveness of two self-managed CBT interventions (cCBT and bibliotherapy) compared to a CBT waiting list in the management of OCD patients in the short term at 3 month follow up
2. The clinical and cost effectiveness of self managed therapies plus conventional CBT compared to waiting list plus conventional CBT at 6 and 12 month follow up
3. Determine patient compliance and patient and health professional acceptability of the two self managed therapy packages (cCBT & GSH).

We will randomise patients to i) cCBT, ii) bibliotherapy (guided self help) or iii) CBT waiting list.

The primary outcome will be OCD symptoms as measured by the Yale Brown Obsessive Compulsive Checklist YBOCS [12] observer-report version. Secondary outcomes will include self-reported health-related quality of life (SF-36), self-reported OCD symptoms (YBOCs self-rated), generic mental health (CORE-OM), depression (PHQ9), anxiety (GAD-7), functioning (WSA), health-related quality of life (EQ5D), employment status (IAPT Employment Status questions A13 –A15), patient satisfaction (CSQ), attachment (RSQ), Perceived Criticism (PCS), expressed emotion (FEICS), patient progression through mental health service (Pathway questionnaire),patient and therapist acceptability (qualitative interviews), and % patients not improved or partially improved and requiring more intensive CBT. Participants will additionally be asked to complete a demographic questionnaire at baseline.

Our preferred primary outcome point was at 6-months follow-up. However, the results of our pilot phase determined identified that this will need to be limited to 3-months as the vast majority of patients had commenced CBT treatment by this point. The primary outcome point will thus reflect CBT waiting lists at the time of study, and as such will enable us to determine an estimate of short term effectiveness of the self-managed therapy packages compared to a CBT waiting list control. This design will not require patients within the trial to have restricted access to treatment beyond that already associated with resource limitations at each site.

At 6 and 12 months follow–up we would expect participants randomised to the waiting list to have accessed conventional CBT and participants randomised to one of the self managed packages (either cCBT or bibliotherapy) will have either remained on the waiting list and accessed conventional CBT or improved sufficiently with the self managed package that they no longer require conventional CBT. The 6 and 12 month follow-up points will enable us to provide a pragmatic demonstration of the clinical and cost-effectiveness of self-managed therapy plus or minus conventional CBT versus waiting-list followed by conventional CBT in the longer term. We will be able to explore a number of longer term outcomes i.e. a) do patients who access self managed therapies improve in the short term but relapse in the longer term, or b) do patients who access self-managed therapies maintain longer term outcomes and have less need for conventional CBT than those who remain on a waiting list prior to conventional CBT. These results will provide critical information concerning the longer term role of self-managed therapy packages for OCD compared to usual care with conventional CBT.

Potential participants (identified through screening waiting lists by a researcher at each of our sites, or through direct referral from professionals or direct advertisement to patients) will be invited to a telephone eligibility screen. If a participant meets the eligibility screen the researcher will give further details of the trial, send information leaflets and a consent form by post and offer them a face to face appointment (either in the clinical site or the patients own home) within 7 days from the telephone screen. At the face to face interview consent and baseline measures will be taken. Follow up interviews at 3, 6 and 12 months may be carried out over the telephone or questionnaires completed and returned by post. This will be dependent on participant preference should they be unable to meet face-to-face.

To ensure the removal of selection bias allocation will be concealed from the researchers completing assessments by randomisation through a central randomisation service. Details of eligible consenting patients will be entered onto a secure web based system administered by the York Clinical Trials Unit, which will then provide the treatment allocation. The system will generate an automatic email to both the site lead and the mental health worker of the participant’s treatment allocation. We have used this method successfully in one completed trial [13] and an ongoing mental health RCT [REEACT: the Randomised Evaluation of the Effectiveness and Acceptability of Computerised Therapy; NIHR HTA, PI [name]]. Allocation will involve minimisation on four important factors: OCD severity (moderate/severe), anti-depressant medication (yes/no), depression (mild/moderate/severe) and chronicity (duration of OCD – 0—5 years/ 6-10 years/ 10 years and over), with the aim of ensuring a balance across treatment arms.

To reduce detection bias, we will aim to blind researchers undertaking outcome assessments to participants’ treatment allocation. To facilitate blinding, we will use the following procedures: 1) ensuring that the outcome assessments conducted by research workers are completed on different days or locations from the clinical areas in which treatment is being conducted; and 2) asking participants to refrain from revealing their treatment allocation at follow-up assessments. Finally we will test blinding by asking research workers to guess the treatment allocation of the patient at each follow-up and to record the number of patients who inadvertently reveal their treatment allocation.

***Concurrent Process Evaluation:*** Criticism has been aimed at RCTs which only focus on pre-specified health outcomes [14]. Process evaluation within trials is recommended to examine key issues such as implementation, acceptability and feasibility which add to the understanding of the RCT results. This study will conduct a process evaluation to explore the barriers and facilitators of implementation by examining the extent to which: i) patients comply with treatment and ii) patients and health professionals find treatment acceptable.

***i) The extent to which patients comply with treatment***: A key aspect of any treatment is the extent to which users complete their agreed course of treatment including CBT between-session tasks. Treatment compliance will be examined through recording the number of sessions attended, and use of self-help materials. With cCBT we will collect automated recordings of the frequency and duration of cCBT use, and patient self reports of time spent between sessions doing CBT based tasks. In the bibliotherapy arm we will collect number, duration and mode of contact (telephone or face to face) via mental health worker records as well as patient diaries of between session work.

***i) The extent to which patients and health professionals find interventions acceptable:*** Successful implementation of research into NHS practise requires that new interventions are accepted and welcomed by both patients and mental health professionals. The 8-item Client Satisfaction Questionnaire (CSQ) will be administered to all patients at 3 and 6 months to assess acceptability. Qualitative interviews will be conducted at post-intervention with a subgroup of 10% of patients stratified by baseline severity in both active intervention arms of the trial across clinical sites. Patients will be sampled on characteristics including gender, ethnicity & outcome. We expect to conduct approximately 40-48 interviews (11-12 interviews at each site). We will also conduct exit interviews with participants who leave treatment early. A sample of 15-20 health professionals will be interviewed with the aim of exploring potential barriers and facilitators to implementing GSH and cCBT into clinical practice. Participants will be identified from health professionals who are working in our sites, and will include those who are delivering treatments in the trial, and those who work in our sites but are not treating patients as part of our trial, to maximise variation. The CSQ will be used to compare patient satisfaction across the treatment arms and, with other quantitative data, to identify predictors of satisfaction. Interviews will be conducted face-to-face, by telephone or by Skype dependent on participant preference and feasibility. Acceptability and exit interviews will be transcribed verbatim and data will be analysed using a framework analysis. An initial coding framework will be developed and transcripts checked against the framework to ensure that there are no significant omissions. Codes in each interview will be examined across individual transcripts as well as across the entire data set and allocated to the framework. Using aspects of the constant comparative method of analysis broader categories using linking codes will be developed across interviews. Data will be interpreted and analysed within the framework to structure patients’ views about each intervention and reasons for leaving the intervention early.

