**3.8 Proposed sample size:**

Three pair-wise comparisons are planned between (i) self-managed therapy packages (cCBT v bibliotherapy), (ii) CBT waiting list and cCBT (iii) CBT waiting list and bibliotherapy.

In trials of non-pharmacological interventions it is recommended that variation between care-providers is considered in sample size estimation and statistical analysis. In this trial there could be variation by therapist (mental health workers) in the two self-managed therapies. For the comparisons of CBT waiting list with cCBT or bibliotherapy we have assumed between therapist variation in the active treatment corresponding to a partially-nested design [17]. For the comparison of cCBT v bibliotherapy the same set of therapists will "supervise" both interventions so the trial is therefore a cross-design [17]. Sample size is estimated using the methods described by Walwyn & [name] [17].

We are not aware of directly relevant estimates for intra-cluster correlation coefficient (ICC) for therapist required for sample size for comparison (ii) & (iii) or the ICC between treatments within therapist for comparison (i). We expect the ICC between treatments within therapist to be less than half the ICC between therapists. With a total sample size of 432 clients and 24 therapist (average of 6 therapists per clinical site) each with a caseload of 6 cCBT and 6 bibliotherapy clients the trial will have a power greater than 80% to detect a difference of 3 YBOC points for each comparison provided the ICC for therapist does not exceed 0.06 and the ICC for treatment within therapist does not exceed 0.015. This calculation assumes a 85% follow-up rate to 6 months (87% was achieved within [name] et al [1]), a 1.67% significance level to maintain a 5% sig level for three pair-wise comparisons, SD for the primary outcome YBOC at 6 months of 7.3 unit, a correlation between baseline YBOCS and 6 month YBOC of 0.43 [1]. In the event that the ICC for therapist is less than 0.1 and the ICC for treatment within therapist is less than 0.05 (which would represent unexpectedly large values), the power is still greater than 75%. By virtue of involving a comparatively large number of therapists the trial is therefore robust again larger ICC values for therapist.

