**3.9 Recruitment strategy:**

Our trial will recruit a minimum of 432 patients with OCD across four clinical sites (assuming a 15% attrition rate, total N=368) with each site recruiting patients over a 27 month recruitment period (including the 9-month pilot phase). All sites will be recruiting from both primary and secondary care services (i.e. in some primary care services high intensity therapists offer full CBT and refer onto secondary care if patients fail to improve while in other services people with OCD are immediately referred to CBT delivered in secondary care). Referral rates for all the clinical sites for people with OCD range from between 60-100 patients per year. In a previous study of psychological treatment with OCD 76% of people referred for the study were randomised [1]. Each site has a designated site lead Manchester ([name]), Norwich ([name]), York ([name]), and Sheffield ([name]). To ensure recruitment we have checked waiting lists in both primary and secondary care in our clinical sites and waiting lists range from 4 to 18 months. Strong links are in place on all sites between clinical and academic staff and three of our four sites have an applicant currently treating people with OCD which will further enhance engagement with recruitment sites. In the lead site in Manchester we have had discussions with the MHRN regarding recruitment with this study if successful. The MHRN (NW hub) includes 6 NHS Trusts (including Manchester Mental Health and Social Care NHS Trust) serving a population of 3.45 million. We have agreed that if funded we will recruit from all 6 NHS trusts and to assist with recruitment in this large geographical area clinical support officers (CSOs) will be trained to conduct telephone eligibility interviews with potential participants. Of the 6 trusts in the NW hub we have agreement in principle from 4 of the NHS Trusts to host the research. We will also apply for adoption by the Mental Health Research Network and link with the Primary Care Research Network to assist with recruitment from PCTs in our clinical sites to ensure that we fulfil our recruitment target. We have a proven track record in recruiting to trials on time and within specified targets [1,18]. Our trial of cCBT uses the support network outlined above and is currently recruiting ahead of target. We have included support costs agreed and negotiated with services to compensate for any additional time involved in the process of recruitment. To meet our recruitment target we will need to recruit 17 patients per month across our 4 sites with a site recruitment target of 4-5 patients per month at each site.

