**3.10 Statistical analysis:**

A full statistical analysis plan for the analysis of primary and secondary outcome measures including any sub-group analyses will be prepared and presented to the TSC (Trial Steering Committee) prior to the commencement of the trial analysis. During the recruitment and follow-up period regular reports will be prepared for the TSC/DMEC on data quality.

Statistical analysis of outcome will follow intention-to-treat principles: patients will be analysed according to randomised group and outcome data will be sought and included in the analysis for all patients irrespective of completion of treatment. Preliminary statistical analysis will model the pattern of missing data in terms of baseline characteristics of patients.

Statistical analyses of the primary outcome measure, YBOC at 3 months, will be based on a mixed model analysis with random effects for therapist and covariates including baseline YBOC and variables potentially predictive of outcome including minimisation variables. This will be used to compare all three arms. Conditional on significance at a 5% level, pairwise comparisons between arms will be carried out using a Bonferroni corrected p-value. Similar analyses will be carried out for quantitative secondary outcomes. A logistic mixed model will be use to compare the percentage of patients requiring full CBT between treatment adjusted for baseline severity.

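### Site is left out of the minimisation and is not named in the models, the logistic model leaves out most allocation factors, and the minimisation levels are not cleanly defined

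*Protocol*

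**What the plan says.** **Allocation (Protocol 3.3.2).** The list is closed: "Allocation will involve minimisation on four important factors: OCD severity (moderate/severe), anti-depressant medication (yes/no), depression (mild/moderate/severe) and chronicity". Chronicity has three levels, the upper two written as "6-10 years/ 10 years and over". Allocation is central, web-based and concealed.

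**Analysis (Protocol 3.10).** The primary outcome is analysed by a "mixed model analysis with random effects for therapist and covariates including baseline YBOC and variables potentially predictive of outcome including minimisation variables". Quantitative secondary outcomes are treated similarly. For the percentage needing full therapy: "A logistic mixed model will be use to compare the percentage of patients requiring full CBT between treatment adjusted for baseline severity". Detail is deferred: "A full statistical analysis plan for the analysis of primary and secondary outcome measures including any sub-group analyses will be prepared".

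**Site structure.**
- Section 3.3.1 gives four sites and asks that waiting times be assessed at each.
- Section 3.8 plans "24 therapist (average of 6 therapists per clinical site) each with a caseload of 6 cCBT and 6 bibliotherapy clients".
- Section 3.9 reports that "waiting lists range from 4 to 18 months".
- Sections 3.3.2 and 3.12 make the observer-rated YBOCS the primary outcome. Section 4 gives the follow-up assessments to site research workers, and section 8 funds one such worker per site.

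**The concern.** Site carries several things that can move the outcome: the therapist pool, the outcome rater and the local service. Nothing in the allocation scheme keeps the arms balanced within site. The commitment in section 3.10 to adjust for minimisation variables does not bring site in, because site is not one of them.

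The therapist random effect is only a partial substitute. Therapists work within sites, so it can absorb site differences in the cCBT and bibliotherapy arms. The waiting-list arm has no trial therapist, so site variation there stays in the residual. Two of the three planned comparisons involve that arm.

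The logistic model is stated with one adjustment. Antidepressant use, depression and chronicity are also used to allocate patients, but are absent from the stated model.

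The level definitions are a separate matter. A patient with exactly 10 years of OCD fits two chronicity levels. Section 3.6 does not require depression for entry, yet the three depression levels do not say where a patient without it is placed. Staff then need an unwritten rule for a variable that feeds both the allocation and the primary model.

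At stake are some precision, exposure to chance imbalance by site, and consistent coding. The validity of the randomisation is not in question.

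**Working it through.** **Inputs.** From Protocol 3.8: N = 432, 24 therapists, 6 patients per therapist in each active arm, difference 3, SD 7.3, baseline correlation 0.43, follow-up 85%, significance level 0.0167, ICCs 0.06 and 0.015. From 3.3.1: four sites. Assumed: equal sites (432/4 = 108), equal arms (24 × 6 = 144), a two-sided test and a normal approximation.

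**1. The plan's own power**
- Adjusted variance: 7.3² × (1 − 0.43²) = 43.44, so SD 6.59.
- Analysed per arm: 144 × 0.85 = 122.4. Analysed per therapist and arm: 6 × 0.85 = 5.1.
- Active arm against waiting list: variance = (43.44/122.4) × [1 + (1 + 4.1 × 0.06)] = 0.797, SE 0.893, power = Φ(3/0.893 − 2.393) = 83.3%.
- cCBT against bibliotherapy, taking 0.015 as the between-treatment ICC within therapist: variance = 2 × (43.44/122.4) × (1 + 4.1 × 0.06 − 5.1 × 0.015) = 0.830, SE 0.911, power 81.6%.

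Both agree with the stated figure of more than 80%.

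**2. Arm counts at a site without site balancing**
- With arm totals held at 144, the count of one arm among 108 patients has variance 108 × (1/3) × (2/3) × (432 − 108)/(432 − 1) = 18.0, so SD 4.2 around 36.
- Simulation gives a 95% range of 28 to 44. The mean gap between the largest and smallest arm within a site is 8.7 (95th percentile 17).

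**3. Cost in power**

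For a site-adjusted contrast of two arms with site counts a and b, variance inflation = 72 / Σ[ab/(a + b)], where 72 is the sum under perfect balance (4 × 36 × 36/72). Over 5,000 simulated allocations the mean is 1.011 and the 97.5th percentile 1.035.

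| Comparison | Balanced | Mean imbalance | 97.5th percentile |
|---|---|---|---|
| Active v waiting list | 83.3% | 82.9% | 81.9% |
| cCBT v bibliotherapy | 81.6% | 81.1% | 80.1% |

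The loss is about 0.5 point on average and about 1.5 points at the bad end.

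**4. Chance difference if site is not adjusted for**

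The documents give no between-site SD, so 1 to 2 YBOCS points is assumed. The difference between two arm counts at a site has variance 3 × 18.0 = 54.1. Over four sites, the SD of the chance arm difference is √(4 × 54.1)/144 = 0.102 per point of site SD. That is about 0.10 to 0.20 points (simulation 0.105 and 0.207), against √(2 × 43.44/122.4) = 0.84 for the SE before clustering.

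**5. Therapist caseload, a separate mechanism**

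If the 72 active patients at a site fall at random into 12 therapist-by-arm cells, caseload has mean 6, SD 2.3 and coefficient of variation 0.39. With design effect 1 + [(1 + 0.39²) × 5.1 − 1] × ICC, power against the waiting list goes from 83.3% to 82.5% at ICC 0.06, and from 80.3% to 78.8% at ICC 0.10.

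**6. Levels**

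Exactly 10 years satisfies both the second and the third chronicity level. For depression, section 3.3.2 gives no cut-offs and no level named for absence of depression.

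**The case against.** The strongest reply is that omitting centre from the minimisation is a legitimate design choice. Allocation is central and concealed, so no bias arises in expectation, and the working shows little loss of power. All of that stands, and it limits the priority. It does not remove the point, because a later analysis plan cannot supply an allocation factor.

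Several stronger readings are tempting and should not be drawn:

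- **That site is excluded from the primary model.** The covariate list in 3.10 is open and a full analysis plan is promised. Site is unnamed, not ruled out. That plan could also extend the logistic model, but the protocol's own statement of that model names one adjustment.
- **That the 4 to 18 month waits are differences between sites and confound the primary result.** Section 3.9 gives the range across primary and secondary care without attributing it to sites, so the spread may lie within sites. All these waits exceed the 3-month primary time point, and section 3.7 asks participants to wait out the 12 weeks. Nor do the documents show that site waiting time drives the need-for-CBT outcome, which section 3.3.2 frames as insufficient improvement.
- **That the chronicity overlap causes imbalance by site or caseload.** The two are unrelated.
- **That minimising on site would secure caseloads of 6 and 6.** Caseload depends on how patients are assigned to therapists within a site, which the protocol does not describe.
- **That site arm counts would range over 27 to 46.** That uses a binomial SD of √(108 × 1/3 × 2/3) = 4.9 and ignores the fixed arm totals.
- **That durations between 5 and 6 years have no level.** The notation is ordinary for whole years, and the protocol does not say that fractions are recorded.

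It is also possible that the mild depression level is meant to include no depression. The protocol does not say so, and that is the extent of the complaint.

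**Conclusion.** The point holds as one of minor-to-moderate priority. The closed list of minimisation factors omits site in a four-site trial where therapists, raters and waiting lists are local. Section 3.10 does not name site, and its therapist effect cannot cover the waiting-list arm. The logistic model as stated leaves out three of the four allocation factors. One chronicity boundary overlaps, and the depression levels are not shown to be exhaustive.

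The size is small: about 0.5 power point on average and up to about 1.5, with power still above 80% at the planned ICCs. If site goes unadjusted, the chance arm difference has an SD of at most about 0.2 points against an SE of 0.84.

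These figures rest on equal sites, fixed equal arm totals, a normal approximation and, for the last one, an assumed site SD of 1 to 2 points. A cautious t reference on 22 degrees of freedom puts the waiting-list comparison at 77.2% even with perfect site balance, so that shortfall is not a consequence of omitting site.

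**What to change.** 1. In section 3.3.2, add site as a fifth minimisation factor for all remaining allocations, with the site of patients already randomised loaded into the central system.
2. In section 3.10, fit site as a fixed effect in the primary, secondary and logistic models, and adjust the logistic model for all minimisation factors.
3. Make the levels mutually exclusive and exhaustive, for example up to 5 / more than 5 and up to 10 / more than 10 years for chronicity, and none-or-mild / moderate / severe for depression. State how patients already entered at the ambiguous values are coded in the analysis.

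The cost is three degrees of freedom for site, slightly looser balance on the existing factors, and a minor amendment during recruitment. Section 3.3.2 already reports pilot results, so some patients have been allocated under the present rules. If recruitment has closed, items 2 and 3 still apply to the analysis. Equal therapist caseloads would need a separate rule for assigning patients to therapists within a site.
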